**Fig. 1 Fig1:**
[figure not shown]
Experimental design. VO2peak, – maximal oxygen uptake; AT, - anaerobic threshold; HR, - heart rate; RPE, - the rate of perceived exertion

### Characteristics of participants

The inclusion criteria will be (1) participants aged between 30 and 69 years old and convalescent from COVID-19 (having the test with a positive diagnosis), (2) having moderate to severe symptoms, and (3) approximately 30 days since recovery from clinical signs or medical discharge (if they had been hospitalized). The exclusion criteria will be (1) exposure to high-altitude places > 1500 m in the last 3 months, (2) significant physical limitations to carry out assessments or intervention, (3) acute or chronic clinical illnesses without medical supervision, (4) anemia, (5) use of immunosuppressive drugs, (6) pregnant women, (7) hormone replacement, (8) smokers, (9) excessive use of alcohol or drugs, (10) three absents in sequence during the intervention, and (11) taking part in less than 75% of the total sessions planned.

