### Design and setting

The study design is based on a randomized, double-blind controlled clinical trial composed of four groups. The control group being formed by the participants who are not available to participate in the intervention and accept to carry out a follow-up through the evaluations; and the physical training groups randomly divided according to the association of training (T) and recovery (R) with hypoxia (H) or normoxia (N): (a) T_H_:R_H_, (b) T_N_:R_H_, and (c) T_N_:R_N_. The allocation ratio will be 1:1:1:1.

As Fig. 1 shows, the experimental protocol will consist of (i) familiarization and carrying out the initial assessments (evaluation 1) in the three sessions of week 0; (ii) 8-week intervention with a partial assessment to adjust the training load on week 5 (half of the intervention – evaluation, (2) (iii) reassessments on week 9, following the end of physical training intervention (evaluation 3), and (iv) reassessments on week 13, four after the end of the intervention (evaluation 4).

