### Sample size

For sample size estimation for clinical trial study design, using sample size estimation as comparing parallels groups (such as three training groups: (a) T_H_:R_H_, (b) T_N_:R_H_, (c) T_N_:R_N_), and control group. A power function of 80% will be used, a level of significance of 5% and an average difference between groups of 10% will be estimated. Based on the formula described previously [40], the sample size required per group is 20. Hence, the total sample size required is 80 for the four groups, considering a drop-out rate of 10%, so the total sample size required is 88, that is, 22 individuals in each group [41].

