### Recruitment

The invitation will be made to the Health Institutions to offer the possibility of participating in this research to patients who have had moderate to severe symptoms approximately 30 days after the recovery of clinical signs or medical discharge (hospitalized people). Furthermore, the disclosure will happen for the entire population of Ribeirão Preto, SP, Brazil, and the region through the local television channels, USP’s local radio and news from the internet, social networks, and among other media outlets. Participants will be asked to complete the evaluations on week 0. After that, they will be assigned randomly to each group. This study will develop every effort to control confounding variables. Randomization and allocation will be performed by the research coordinator. Considering special randomization techniques, in this project, we will be using the randomization of matched pairs [42], considering a baseline pairing strategy regarding confounding variables such as sex, age, and level of physical conditioning of the participants for their selection and random assignment in the research groups. As there are three training groups, (a) T_H_:R_H_, (b) T_N_:R_H_, and (c) T_N_:R_N_, pairing groups will be organized consisting of participants based on the matching characteristics above, which will be drawn randomly using Microsoft Excel for allocation to groups. This method is satisfactory and suitable for intervention studies in which there are not many participants. In terms of blinding, only the research coordinator is aware of the allocation. Different researchers will work on the intervention and collect information from the participants as evaluations, who will be blinded to avoid potential bias. To maintain the overall quality and legitimacy of the clinical trial, unblinding should occur only in exceptional circumstances when knowledge of the actual treatment is essential for further management of the patient.

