### Statistical analysis

After double data entry, an exploratory analysis of the data will be carried out. The primary objective will be to summarize the values, organize, and describe the data through tables with descriptive measures and graphs. Continuous variables will be expressed in terms of basic descriptive statistics (mean, median, and standard deviation), whereas categorical variables will be described in terms of frequency and percentage. The effects of the different types of training (hypoxia and normoxia), before, after 8 weeks, and after 4 weeks after the intervention, for continuous outcomes will be compared using a linear regression model with mixed effects (fixed and random). If there are binary outcomes, a cox proportional hazards model will be used to estimate the incidence rates and their respective confidence intervals, including potential confounders as covariates. The possible associations between hematological, immunological, autonomic, aerobic, and anaerobic variables will be verified with hypothesis testing and the use of other regression models. In the case of handling missing data, we will use statistical methods as multiple imputation or Bayesian methods. The level of significance will be set at 5% in all analyses.

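### Two attendance rules that can only be met after allocation are listed as exclusion criteria, so the plan as written removes randomised participants from the training arms and puts the VO2peak comparison at risk of bias

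*Protocol article*

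**What the plan says.** In the protocol article, Characteristics of participants gives a single list of exclusion criteria. It opens with a baseline condition, "The exclusion criteria will be (1) exposure to high-altitude places > 1500 m in the last 3 months", goes on through others such as anemia and smoking, and ends with "10) three absents in sequence during the intervention, and (11) taking part in less than 75% of the total sessions planned".

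Recruitment says that participants first complete the week 0 evaluations and adds: "After that, they will be assigned randomly to each group". For the three training groups the draw is made within matched sets: "pairing groups will be organized consisting of participants based on the matching characteristics above".

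Design and setting describes the fourth group differently: "The control group being formed by the participants who are not available to participate in the intervention". That group has no training sessions.

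Sample size allows for losses as follows: "considering a drop-out rate of 10%, so the total sample size required is 88". On missing data, Statistical analysis says "we will use statistical methods as multiple imputation or Bayesian methods", without saying whose data this covers.

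**The concern.** An exclusion criterion normally screens people before allocation. These two act during the 8-week programme, on people already assigned to one of the three training arms. Removing them makes membership of the compared groups depend on something that happened after randomisation and that the allocated condition may have influenced.

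The article itself gives a reason why attendance could differ by arm. Its Discussion says that hypoxia can lower exercise intensity and uses this to justify having two hypoxia arms. If tolerability affects attendance, and poor attenders would also have responded differently, the arms that remain are no longer comparable on the primary outcome. Removals also break up the matched sets and reduce the number analysed.

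The control group cannot be filtered in this way. It is already non-randomised, so the rules add a further selection, on the trained side only, to a contrast that randomisation never protected.

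**Working it through.** **Timing.** Assignment follows the week 0 evaluations and training starts afterwards. Three absences in a row, or attendance below 75%, can only be observed during training. Everyone in a training arm who meets either rule has therefore been randomised.

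**Reach of the two rules.** Three sessions a week for 8 weeks is 3 × 8 = 24 sessions.
- 75% attendance is 0.75 × 24 = 18 sessions.
- One missed week is three absences in a row and leaves up to 21/24 = 87.5% attendance. Rule 10 removes this person and rule 11 would keep them.
- Seven scattered absences leave 17/24 = 70.8%. Rule 11 removes this person and rule 10 would keep them.

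**The plan's own figure.** 4 × 20 = 80 and 80 × 1.10 = 88, or 22 per group, as stated. (Dividing by 0.90 gives 89.) The allowance is 22 − 20 = 2 people per group.

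**Implied SD (assumption).** No SD is given. With a 10% difference, 80% power, two-sided 5% and 20 per group, SD = 10 × √(20/2) / (1.960 + 0.842) = 11.3% of the mean. The bias illustration below uses 11%.

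**Removals against the allowance (illustration).** If each of the 24 sessions is attended independently with probability p, the exact chance of meeting either rule is:

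| p | removed | left of 22 |
|---|---|---|
| 0.95 | 0.3% | 21.9 |
| 0.90 | 2.5% | 21.5 |
| 0.85 | 9.8% | 19.8 |
| 0.80 | 24.7% | 16.6 |

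At 85% the rules alone use up the allowance. With SD 11.3%, power is about 76% at 18 per arm and 71% at 16. If absence instead comes in whole weeks, with chance w in each week, rule 10 removes 1 − (1 − w)^8: 3.9%, 7.7% and 14.9% for w = 0.5%, 1% and 2%.

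**Bias under no true effect (illustration).** Suppose the lowest fraction q on an attendance trait is removed, and the trait has correlation r with the outcome. The mean of those kept shifts by r × φ(z_q)/(1 − q) SDs. The factor φ(z_q)/(1 − q) is 0.195, 0.350 and 0.497 for q = 10%, 20% and 30%. With SD 11% and 20 per arm, the standard error of a difference is 11 × √(2/20) = 3.48. Type I error comes from the noncentral t distribution with 38 degrees of freedom.

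| Removed, arm v comparator | Shift, r = 0.3 | Shift, r = 0.5 | Type I error |
|---|---|---|---|
| 20% v 0% | 1.2 | 1.9 | 6.2% to 8.4% |
| 30% v 0% | 1.6 | 2.7 | 7.5% to 11.9% |
| 20% v 10% | 0.5 | 0.9 | 5.2% to 5.7% |
| 30% v 10% | 1.0 | 1.7 | 5.9% to 7.5% |
| equal removal, same r | 0 | 0 | 5% |

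Shifts are in percentage points of mean VO2peak. With r = 0 every shift is zero. The rows with nobody removed from the comparator fit the control contrast best, because the rules act on all three randomised arms.

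**The case against.** The best defence is that the article does not say what exclusion means here: stopping training, leaving the assessments, or being dropped from the analysis. An analysis plan that is not shown may define an all-randomised set. That stands in part, and the lack of an intention-to-treat statement in a condensed article is not the point. The point is a rule that is stated: these people are classed with those who fail entry criteria, and nothing in the article returns them to follow-up or analysis.

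Some features also reduce arm-related absence. Participants are not told the oxygen concentration, load is controlled by lactate, heart rate and perceived exertion, and scheduling is meant to be flexible. These lessen the risk without removing it.

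Four stronger readings are tempting, and the article supports none of them.
- A reader might infer that the two rules contradict each other. They do not: one is triggered by consecutive absence, the other by cumulative absence, and either suffices.
- A reader might infer that the exclusions defeat the planned multiple imputation. The article does not say whose missing data will be imputed, and other losses would still leave data to impute.
- A reader might infer that every training-versus-control contrast is inflated. That contrast was never randomised, and absence could come from returning to work as easily as from poor response, so the direction is unknown.
- A reader might take the error rates near 12%, or the 15% removed, as expected values. The first needs r = 0.5 with 30% removed from one arm and none from the other; the second needs a 2% weekly rate. Neither input is in the article.

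**Conclusion.** The point holds as a badly placed rule that puts the primary comparison at risk. It does not show that the comparison is biased. What is certain from the text is that the two criteria act only after randomisation, only on the training arms, and that rule 10 can remove someone with up to 87.5% attendance.

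The size is conditional. Between randomised arms, moderately unequal removal (30% v 10%) shifts the difference by about 1.0 to 1.7 points, with type I error of about 6% to 7.5%. With 20% to 30% removed from one arm and none from the comparator, the shift is about 1.2 to 2.7 points and the error about 6% to 12%. These figures assume an SD of 11%, 20 per arm and r of 0.3 to 0.5. The shift is zero if removal is equal and equally selected, or unrelated to outcome. The drop-out allowance is at risk if per-session attendance is around 85% or lower.

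**What to change.** Take (10) and (11) out of the exclusion criteria. State that all randomised participants stay in the scheduled evaluations and are analysed in their allocated arm, whatever their attendance. Use the attendance thresholds only to define a supplementary per-protocol set. Report attendance, and any removals with reasons, by arm.

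Trial status reports 84 participants already included. If anyone has been removed under these rules, include their available evaluations and invite them to those that remain. The change concerns follow-up and analysis only; it does not touch the training programme or decisions about continuing it.

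The cost is a wording amendment and some extra follow-up of non-attenders at visits already scheduled. The sample size stays at 88. The estimated effect may be slightly smaller, because it will include people who trained less.

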### Instrumentation normobaric hypoxia

The three training groups, except the control, will carry out the training program in the same way: on bicycles, around the normobaric hypoxia tents (Colorado Altitude Tents, Colorado, USA) using the individual system that includes the face mask. Thus, participants will not be aware of the O_2_ concentration in the air contained in the tent in which they are positioned. This procedure will be done to minimize possible psychological influences from exposure to hypoxia.

A system that includes an individual face mask to be worn in the training program has been developed. Each participant will receive a mask for exclusive use in the initial evaluations and be instructed to wear it during the entire intervention aiming to work at the highest level of safety. Fig. 2 illustrates the strategy that will be used for the intervention. The normobaric hypoxia tents with O_2_ concentration control will be set up at the Multisport Gymnasium at the University. This space has good air circulation, and the bikes will be positioned around the tents, respecting 3 m between each bike. Up to eight participants will breathe the air in the normobaric hypoxia tents through hoses and an individual system that includes the mask. Two tents will be used simultaneously, enabling the training of up to 16 participants per period.

**Fig. 2 Fig2:**
[figure not shown]
Strategy for training participants

Each system will consist of a face mask of personal protective equipment with membranes that will allow only the inspired air to enter the upper cavity (nose) and only the exhaled air to exit the lower cavity (mouth). This membrane system will prevent air from being exhaled through the upper cavity, thus avoiding the possibility of contamination of the air contained in the tent, or else, inspired by the lower cavity, avoiding that the ambient air is inspired in this case, which would decrease the precision of the study. A safety valve will be used on the bottom of resuscitation bags to increase this strategy’s efficiency and facilitate the hose connection that will take the air from the normobaric hypoxia tent to the individual system (mask). The system will be covered with neoprene protection to provide greater comfort and stability during physical training (Fig. 3).

**Fig. 3 Fig3:**
[figure not shown]
Individual mask for training participants

### Intervention protocol

The moderate training sessions in bicycles will be performed with a frequency of 3 times a week and consist of three parts (warm-up, main part, and cool down) with a total duration of up to 50.5 min. The initial stage (warm-up) and the final stage (cool down) will last for 5 and 3 min, respectively, and will be of low intensity, corresponding to “easy” by the rate of perceived exertion (RPE). The training intensity in the main part will be based on the AT values. Blood lactate concentration [La-], target heart rate, and RPE will control the load. The training will consist of sets with efforts lasting 5 min with an intensity close to the upper limit of training zone 2 (90–100% of AT) with a passive pause of 2.5 min between efforts. Training loads will be increased during the first 4 weeks, as it is explained in Table 1.

**Table 1 Tab1:** Training dynamics week by week, the progression of the load, the total volume of each session, and internal training load (Trimp)

Training dynamics	W1	W2	W3	W4-W8
Number of sets	3	4	5	6
Efforts (min)	5	5	5	5
Time recovery between efforts (min)	2.5	2.5	2.5	2.5
Total volume of each session (min)	28	35.5	43	50.5
RPE	5	5	5	5
Trimp (AU)	140	177.5	215	252.5

*W* week, *RPE* the rate of perceived exertion, *AU* arbitrary units

Additionally, the internal training load (Trimp) will be quantified at each session. It will be assumed as the product between the duration of the session (minutes) by the RPE values, the results being expressed in arbitrary units (AU). The RPE will be presented after the end of each training session [37]. This procedure will monitor possible differences in the absolute internal load among the T_H_:R_H_, T_N_:R_H_, T_N_:R_N_ groups. An estimative is presented in Table 1 with a fixed RPE value of 5.

It is important to highlight that despite the intensity of the sessions being considered “moderate” and, theoretically allowing participants to carry out the proposed training continuously, we believe that the inclusion of 2.5 min between efforts, that is, an effort: pause relationship of 2:1 will allow less discomfort during efforts, without, however, compromising the aerobic “gains” from this training model. Other necessary adaptations will be made according to the performance and needs of each participant. The final part (cool down) will last for 3 min with “easy” intensity by the RPE.

Out of the three training groups, two will be exposed to hypoxia according to the association of training (T) and recovery (R) with hypoxia (H): (a) T_H_:R_H_ and (b) T_N_:R_H_. These groups will be subjected at an inspired fraction of O_2_ (FiO_2_) to simulate approximately 3000 m of altitude in the Multisport Gymnasium. The other training group will train in normoxia (T_N_:R_N_) at FiO_2_ corresponding to sea level in the Multisport Gymnasium. Hypoxia generators will be used together with the normobaric hypoxia tents. It is important to note that O_2_ saturation will be monitored during all training sessions, which will allow us to verify the response to hypoxia during training and the application of the Lake Louise Scale.

All sessions will be developed with a group of researchers and monitored by acute responses to the training using HR, blood oxygen saturation (SPO_2_), and RPE. Weekly, acute responses will be associated with exposure to hypoxia using a questionnaire. These data will be analyzed as soon as they are collected to provide the highest safety to the participants. Any unexpected responses will be communicated to the study’s coordinator, who will be available at all the time used for intervention and evaluations. In addition, on weeks 2, 4, and 6, the blood [La-] will be evaluated to control the training load.

### Acute responses

#### Blood oxygen saturation (SPO_2_)

Blood O_2_ saturation will be monitored using a pulse oximeter (G-Tech Portable). The equipment will be positioned on the participants’ distal phalanx during training, and the measurements will be recorded in four moments, id. est., rest, end of each stimulus, lowest result during the break, and end of the pause.

#### Rate of perceived exertion (RPE)

The training intensity will be controlled by RPE [38].

#### Acute responses associated with exposure to hypoxia

Both training groups (normoxia and hypoxia) will answer this questionnaire to maintain the impartiality of the study. The Lake Louise Score [39] will be used. There is no intention to diagnose acute mountain disease but verify and monitor the acute responses to hypoxia exposure.

#### Blood lactate concentration [La^-^]

Blood [La-] will be determined using the YSI 2300 STAT analyzer (Yellow Springs, OH, USA). For this, 25 μL of whole blood will be collected from the earlobe, using previously calibrated heparinized capillaries. Blood samples will be immediately homogenized in microtubes containing 1% sodium fluoride.

### Outcomes

The primary outcome is the maximum oxygen consumption (VO_2_peak). The secondary outcomes include lung function, inflammatory mediators, hematological, autonomic parameters, AT, body composition analysis, quality of life, mental health, anthropometric measurements, and physical fitness. All outcomes will be assessed at baseline, immediately post-intervention, and later, 4 weeks after the end of the intervention. After 4 weeks, the primary and some secondary outcomes will be assessed (partial evaluation). The primary and secondary outcomes will be presented by mean and standard deviation.

### Participant timeline

This study is ongoing and started in September 2020, ending in December 2021. The schedule for enrolment, interventions, and assessments is presented in Table 2.

**Table 2 Tab2:** Schedule of enrolment, interventions, and assessments

Timepoint	Study period					
	Enrolment	Allocation	Post-allocation			
	***-t***_***1***_	0	***Baseline***	***Partial evaluation*** ***(week 5)***	***Post-training*** ***(week 9)***	***After 4 weeks of training end (week 13)***
**Enrolment**						
**Eligibility screen**	X					
**Informed consent**	X					
**Allocation**		X				
**Interventions (training)**						
***Normoxia (N)***			X			
***Hypoxia (H)***			X			
***Hypoxia recovery (HR)***			X			
***Control group***			X			
**Assessments**						
***Lung function (spirometry)***			X	X	X	X
***Autonomic parameters (HRV)***			X	X	X	X
***Max Aerobic power (VO***_***2***_***peak)***			X	X	X	X
***Anaerobic threshold***			X	X	X	X
***Inflammatory mediators***^***1***^			X		X	X
***Haematological parameters***^***2***^			X		X	X
***Body composition (iDXA)***			X		X	X
***Quality of life (SF – 12)***			X		X	X
***Mental Health (DASS–21)***			X		X	X
***Anthropometric (BMI, WC)***			X		X	X
***Physical fitness (motor tests)***			X		X	X

*HRV* heart rate variability, *max* maximum, *BMI* body mass index, *WC* waist circumference

^1^Inflammatory mediators include quantification of cytokines and profile of eicosanoids

^2^Haematological parameters include complete blood cell count, total cholesterol, triglycerides, HDL-c, LDL-c, lactate dehydrogenase, liver enzymes (alanine aminotransferase and aspartate aminotransferase), and EPO

